### Primary outcomes

2.9

#### Hwabyung scale

2.9.1

The Hwabyung scale (40) will be used to assess Hwabyung-related personality and symptoms. This scale comprises 16 items on Hwabyung personality and 15 items on Hwabyung symptoms. This is a self-reported 5-point Likert scale. The total score ranges from 0 to 64 for Hwabyung personality, and from 0 to 60 for Hwabyung symptoms. Higher scores indicate higher Hwabyung personality and symptoms. In a previous study (40), the Cronbach's alpha for the Hwabyung scale was .85 for Hwabyung personality, .93 for Hwabyung symptoms, and .93 overall.

#### Hwabyung comprehensive test

2.9.2

The Hwabyung Comprehensive Test (41) will be used to assess Hwabyung-related symptoms and psychological characteristics. This test consists of 13 items on Hwabyung symptoms, 5 items on the incident questionnaire, and 21 items on Hwabyung psychological characteristics. Hwabyung symptoms and psychological characteristics will be used to interpret scores. This test is a self-reported 5-point Likert scale. The total score ranges from 0 to 52 for Hwabyung symptoms, and from 0 to 84 for Hwabyung psychological characteristics. Higher score indicates more severe Hwabyung symptoms and vulnerability. In a previous study (41), the Cronbach's alpha for the Hwabyung Comprehensive Test was .89 for Hwabyung symptoms and .95 for Hwabyung psychological characteristics.

#### Hamilton depression rating scale

2.9.3

In this study, a structured interview manual will be used to increase inter-rater reliability.

The Korean version of the Hamilton Depression Rating Scale (42) will be used to assess depression. This is an observer rating scale consisting of 17 items. Each item is scored from 0 to 2 or from 0 to 4. The total score ranges from 0 to 52. Higher scores indicate more depressive symptoms. In this study, a structured interview manual will be used to increase the inter-rater reliability (39).

### Secondary outcomes

2.10

#### Hamilton anxiety rating scale

2.10.1

The Hamilton Anxiety Rating Scale (43) will be used to assess anxiety. This is an observer rating scale consisting of 14 items. Each item is scored from 0 to 4. The total score ranges from 0 to 56. Higher scores indicate higher anxiety symptoms. In this study, a structured interview manual will be used to increase the inter-rater reliability (38).

#### State-trait anger expression inventory

2.10.2

The Korean Adaptation of the State-Trait Anger Expression Inventory (44) will be used to assess anger experiences and expression. This scale consists of 10 items for state anger, 10 items for trait anger, and 24 items for anger expression. This is a self-reported 4-point Likert scale. The total score ranges from 10 to 40 for state anger, 10 to 40 for trait anger, and 24 to 96 for anger expression. Anger expression consists of three factors: anger-out, anger-in, and anger control. Anger control is considered a functional expression of anger and will be reverse calculated. A higher score indicates experiencing and expressing more anger. In a previous study (44), Cronbach's alpha was .90 for state anger, .75 for trait anger, .70 for anger-out, .66 for anger-in and, .79 for anger-control.

#### Integrative vitality scale

2.10.3

The Integrative Vitality Scale is a self-reported questionnaire that is under development to measure physical and psychological vitality. This scale consists of 11 items on physical vitality (e.g., My body is full of energy) and 11 items on psychological vitality (e.g., I have a passion for life). This is a self-reported 5-point Likert scale. The total score ranges from 0 to 44 for physical vitality and from 0 to 44 for psychological vitality. One item (e.g., My head feels heavy and achy) will be reverse-calculated. Higher scores indicate higher subjective vitality. In a survey of 348 people, Cronbach's alpha was .91 for physical vitality, .91 for psychological vitality, and .94 overall (preparing for publication).

### Adverse events

2.11

Adverse events will be assessed after each session of MQT-SH. The results section will describe the type, frequency, and severity of the adverse events. Severity will be assessed according to three grades (mild, moderate, or severe). Mild is defined as an adverse reaction that does not interfere with daily life. Moderate is defined as an adverse reaction that interferes with daily life but is not dangerous. Severe is defined as an adverse reaction that is severe and interferes with basic daily activities (e.g., eating, changing clothes).

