The MQT-SH period may vary depending on the setting (9). A manual for researchers and participants was developed to improve compliance to the intervention protocol. In this study, the MQT-SH will be conducted once a week for 1.5 h for a total of six weeks. Each session will consist of 20 min of education, 40 min of practice (i.e., meditation), and 30 min of group activities, such as checking home training and sharing practice experiences. This intervention will be conducted as a group program, with a maximum of 12 people per group. Participants will be asked to perform home training five times a week for at least 30 min each day. Participants will receive guided audio materials for home training. Dropouts will be defined as i) individuals attending three or less out of six sessions, ii) those who complain of physical or psychological discomfort and want to give up because of such discomfort, or iii) those who would want to give up for reasons other than discomfort.

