#### Wait-list control

2.4.2

The control group will be assigned to WLC and will receive no treatment for the first six weeks. Considering ethical equity, the control group will undergo the same MQT-SH over the next six weeks.

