### Assessment

2.8

Assessments are scheduled at baseline (T1), post-intervention (six weeks; T2), and follow-up (12 weeks; T3). Assessments include observer ratings (conducted by blinded clinicians) and self-report ratings. A structured interview manual will be used to increase the reliability of observer ratings (e.g., 38, 39). If participants drop out, they will not be assessed further. Missing data will be statistically imputed. **Table 2** summarizes the assessment time points.

**Table 2 T2:** Study assessment points.

	Screening	T1	T2	T3
HBDIS	○			
SCID-5	○			
Demographic Information	○			
HS		○	○	○
HCT		○	○	○
HDRS		○	○	○
HARS		○	○	○
STAXI		○	○	○
IVS		○	○	○

T1, baseline; T2, post-intervention; T3, follow-up; HBDIS, Hwa-Byung Diagnostic Interview Schedule; SCID-5, Structured Clinical Interview for DSM-5; HS, Hwabyung Scale; HCT, Hwabyung Comprehensive Test; HDRS, Hamilton Depression Rating Scale; HARS, Hamilton Anxiety Rating Scale; STAXI; State-Trait Anger Expression Inventory; IVS, Integrative Vitality Scale.

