### Conclusion

3.2

In conclusion, this study will provide empirical results on the effectiveness of a standardized mindfulness and Qigong program for patients with Hwabyung and depressive disorder. This study will be an opportunity to investigate the possibility of a low-risk practical treatment for emotional problems in clinical settings.

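### Adverse-event enquiry is scheduled only after MQT-SH sessions, so there is none in the wait-list arm before T2, in the MQT-SH arm after week 6, or after a participant stops attending

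*Protocol article*

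**What the plan says.** Section 2.11 (Adverse events) states: "Adverse events will be assessed after each session of MQT-SH". It promises a description of type, frequency and severity on three grades, and names no other time of collection.

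The sessions themselves are defined in section 2.4.1: "the MQT-SH will be conducted once a week for 1.5 h for a total of six weeks". Between sessions there is further exposure: "Participants will be asked to perform home training five times a week for at least 30 min each day".

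For the control arm, section 2.4.2 says: "The control group will be assigned to WLC and will receive no treatment for the first six weeks". Afterwards "the control group will undergo the same MQT-SH over the next six weeks". The Discussion confirms that the main analysis compares the groups on T1 and T2.

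Section 2.4.1 gives three kinds of dropout: attendance at no more than three of the six sessions, giving up for reasons other than discomfort, and "those who complain of physical or psychological discomfort and want to give up because of such discomfort". Section 2.8 (Assessment) adds: "If participants drop out, they will not be assessed further. Missing data will be statistically imputed".

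**The concern.** Ascertainment depends on being at a session. This has two consequences.

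First, the arms are not asked about adverse events over the same weeks. Patients with Hwabyung and a depressive disorder can be expected to report bodily and emotional complaints whether or not they train. Without the same question put to untreated controls over the same period, a count from the MQT-SH sessions mixes programme effects with background. The error can go either way: background complaints may be read as reactions, or real reactions dismissed as background.

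Second, enquiry ends when attendance ends. Discomfort is itself one of the listed reasons for leaving, so the loss of follow-up may be related to harm. Someone who feels unwell during home training and does not come back has no stated collection point. The imputation planned for the outcomes cannot supply event reports that nobody asked for.

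At stake is how the safety section of the results can be read. The article describes the trial this way: "This study will be an opportunity to investigate the possibility of a low-risk practical treatment for emotional problems in clinical settings".

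**Working it through.** **Inputs.** Six weekly sessions per participant (section 2.4.1). No sessions for controls in weeks 0-6 and the same programme in weeks 6-12 (section 2.4.2). 25 evaluable participants per arm and a 20% dropout allowance, giving 32 per arm (section 2.5).

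**The plan's own figure.** 25 / (1 - 0.20) = 31.25, rounded up to 32 per arm and 64 in total. This reproduces.

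**Scheduled enquiries = participants x sessions, at full attendance.**

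| Period | MQT-SH arm | Wait-list arm |
|---|---|---|
| Weeks 0-6 (randomised comparison) | 32 x 6 = 192 | 32 x 0 = 0 |
| Weeks 6-12 | 32 x 0 = 0 | 32 x 6 = 192 |

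Each arm is asked in one half of the trial only, and the two halves do not overlap.

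**What this means for a frequency.** The article gives no background risk, so assume a six-week risk of 5% to 30%, equal in both arms, meaning no effect of the programme. The expected number of affected participants in the MQT-SH arm is 32 x 0.05 = 1.6 to 32 x 0.30 = 9.6. The scheduled enquiry in the wait-list arm would record 0 throughout. Nothing in the data would show that the MQT-SH figure was all background.

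**After discontinuation.** The allowance leaves room for 32 - 25 = 7 dropouts per arm (20% of 32 is 6.4). If 7 leave the MQT-SH arm:
- after no sessions, 7 x 6 = 42 of 192 enquiries are lost (22%);
- after three sessions, 7 x 3 = 21 of 192 are lost (11%).

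This is the number of enquiries lost, not the size of a bias. The 20% covers all three kinds of dropout, and the article does not say what share would leave for discomfort.

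**With the change under fix.** At full contact there are 32 enquiries against 32 at T2, and the same at T3. The sample size and the primary analysis do not change.

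**The case against.** The strongest reply is that section 2.11 promises a description and not a comparison, that its grades are worded as reactions, which an untreated arm cannot have to MQT-SH, and that no safety hypothesis is stated. Descriptive recording is a legitimate design choice. The article is also condensed: it does not exclude spontaneous reports, and the full protocol may provide for them. The absence of an adverse-event row in Table 2 proves little, because that table also omits the post-session checks that section 2.11 does state. These points stand, and they limit the finding to scheduled enquiry as printed.

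Several stronger readings are tempting, but the documents do not support them:

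- **That worsening in untreated controls goes unseen.** HDRS, HARS and the self-report scales are taken in both arms at T2, with the Hamilton ratings made by blinded clinicians. Worsening in retained controls is measured.
- **That those who quit for discomfort vanish from the safety record.** Events recorded at attended sessions remain, and the team must have heard the complaint to classify the dropout. What is missing is a stated enquiry afterwards and a statement that the complaint is recorded as an adverse event. The rule in section 2.8 stands beside outcome imputation, so applying it to adverse events is an inference; section 2.11 alone gives the same result, since without a session there is no enquiry.
- **That anyone who misses a session is lost.** A person who misses one or two sessions is not a dropout and is asked at the next one attended.
- **That the plan draws a low-risk conclusion it cannot support.** It speaks only of investigating a possibility.

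Controls also receive the programme later, so session-based reports may come from up to 64 treated people. That improves the description but does not supply an untreated rate.

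Finally, the gain from a comparison is modest. With 32 per arm and no control events, a two-sided Fisher test gives p = 0.053 for 5 affected and p = 0.024 for 6. Only a large excess would show, which is why the T2 answers should be reported descriptively.

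**Conclusion.** The point holds as a limited, cheaply repaired weakness. As written, the schedule gives 192 enquiries against 0 in the only randomised comparison, 0 in the MQT-SH arm in weeks 6-12, and none after attendance stops. Session-based frequencies will be uncontrolled and may be incomplete after discontinuation. The direction and size of any resulting bias cannot be derived from the article.

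The conclusion assumes that section 2.11 lists all scheduled collection; the counts assume 32 per arm and full attendance. It bears on what can be said about safety, not on the efficacy analysis or the sample size.

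**What to change.** 1. Keep the post-session enquiry in section 2.11.
2. Add one identical adverse-event question, with the same three grades, at T2 and T3 for all randomised participants in both arms.
3. Have the clinical research coordinator ask it. Section 2.6 already gives the coordinator the allocation, so the blinding of assessors in section 2.7 is kept.
4. Amend section 2.8 so that participants who drop out are still contacted for this question, and state that discomfort leading to dropout is recorded as an adverse event.
5. Report the T2 answers by arm descriptively, noting that MQT-SH participants will have been prompted up to six times before and controls not at all. Report session-based events as uncontrolled.

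**Cost.** An amendment with review by the IRB, a line on the case report form and a few minutes per assessment. Contact with dropouts is a real addition, because the plan now gives them no further visit. Section 3.3 says that treatment has started, so data will be incomplete for participants already past T2; the report should say how many.

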### Data management

2.12

All the data will be encrypted and stored on the researcher's computer. Personally identifiable information will not be included in publications. Personal information will be stored together with the data for a maximum of 10 years, after which they will be destroyed.

### Statistical analyses

2.13

Analyses based on the Intention-To-Treat (ITT) principle will be conducted, with missing data imputed using expectation-maximization (EM) algorithm.

To investigate the effect of MQT-SH, 2 (group: MQT-SH *vs*. WLC) × 2 (time: T1 *vs*. T2) repeated measures ANOVA will be performed. If the interaction between the group and time is significant, a simple main effect analysis will be performed.

Additional analyses will be performed. First, to investigate the follow-up effect of the MQT-SH, a paired t-test will be performed to compare T3 and T1 and T3 and T2 in the experimental group alone. Second, a paired t-test comparing T3 and T2 in the control group will be performed to investigate the effects of MQT-SH. Third, a subgroup analysis will be performed to investigate the difference in effectiveness depending on the amount of home training. For this purpose, 2 (amount: top 30% *vs*. bottom 30%) × 2 (time: pre-intervention *vs*. post-intervention) repeated-measures ANOVA will be performed. Data from both the experimental and control groups will be used for subgroup analysis.

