### Sample size

2.5

The sample size was estimated using G*power (37). The sample size calculation is based on a power of 80% and a type I error of 5%, as well as a moderate effect size for the intervention (partial *η*^2^ = 0.04). A minimum sample size of 25 participants per group is estimated (50 participants in total). This number was obtained by performing a simulation procedure using repeated-measures ANOVA, considering the existence of a significant 2 (group: experimental *vs*. control) × 2 (time: T1 *vs*. T2) interaction effect. Considering a dropout rate of 20%, we aim to include 32 participants per group (64 participants in total).

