### Randomization

2.6

Participants will be randomly allocated to either the experimental or the control group (1:1 ratio, block size = 4). Random numbers for allocation will be generated by the computer and managed by the researcher ([name]). Before enrollment, the participants and other researchers will be unaware of the allocation. After enrollment, [name] will allocate participants to the experimental or control group according to random numbers, and the results of the allocation will be shared only with the clinical research coordinator.

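### EM-filled T2 scores go into an ordinary ANOVA as if observed: type I error is about 9-11% if group is in the EM model, and the effect is diluted by about 20% if it is not

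*Protocol article*

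**What the plan says.** Section 2.8 (Assessment) stops data collection at dropout: "If participants drop out, they will not be assessed further. Missing data will be statistically imputed". A participant who drops out before week 6 therefore has no T2 score.

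Section 2.13 (Statistical analyses) names the method for those scores: "Analyses based on the Intention-To-Treat (ITT) principle will be conducted, with missing data imputed using expectation-maximization (EM) algorithm". The main test follows directly, a 2 (group) × 2 (T1, T2) repeated-measures ANOVA judged on the interaction. The Discussion confirms that the T1-T2 comparison between groups is the main analysis.

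Section 2.5 (Sample size) sets the scale of the problem: "Considering a dropout rate of 20%, we aim to include 32 participants per group (64 participants in total". It plans for 80% power and a 5% type I error.

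The article does not say whether group is a variable in the EM model or whether residual noise is added. It mentions no multiple imputation and no correction of the variance or degrees of freedom.

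**The concern.** EM fill-in replaces a missing score by its expected value given the other variables. Such a value carries no residual scatter and no sign that it was estimated. An ordinary ANOVA cannot tell it from a measurement, so it takes the residual variance as too small and the sample as too large.

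The imputation model also decides what the filled-in scores say about treatment. If it contains group, they repeat the observed group difference and add false precision. If it omits group, dropouts in both arms are predicted from one common regression, which pulls the arms together.

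At stake is the main comparison for every primary and secondary outcome analysed this way: either its significance level, or the size of its estimate and the coverage of its interval.

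**Working it through.** **Inputs from the article.** Partial η² = 0.04, 80% power, 5% type I error, 25 per group evaluable, 32 per group randomised, 20% dropout (section 2.5); 1:1 allocation (section 2.6).

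**Assumptions, not in the article.** T1-T2 correlation ρ from 0.3 to 0.7; normal scores with SD 1 at each visit; T2 missing completely at random, in about equal numbers per arm; EM filling in conditional means.

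**1. The plan's own sample size.** f² = 0.04/0.96 = 0.0417, so f = 0.204. For the within-between interaction in G*Power, λ = f² × N × 2/(1 − ρ) with (1, N − 2) df. At ρ = 0.5 and N = 50, λ = 0.0417 × 50 × 2/0.5 = 8.33 and power is 0.807, so 25 per group is reproduced. (ρ = 0.3 would need 68 in total, and ρ = 0.7 would need 32.) Dropout: 25/0.8 = 31.25, rounded up to 32 per group, 64 in total.

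**2. The effect this implies.** With two visits the interaction test is a t test on T2 − T1, for which λ = δ²N/[8(1 − ρ)]. Equating the two expressions gives δ = 4f = 0.82 SD.

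**3. Degrees of freedom.** 20% of 64 is about 13 missing and 51 observed. The ANOVA uses 64 − 2 = 62 error df; the observed scores support 51 − 2 = 49.

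**4. Group in the EM model: closed-form check.** Take 25.5 observed per arm and a missing fraction of 13/64 = 0.203, and ignore the estimation of the slope.
- True variance of the estimate: 2[(1 − ρ²)/25.5 + (1 − ρ)²/32]. At ρ = 0.5: 2[0.0294 + 0.0078] = 0.0744, SD 0.273.
- Variance the ANOVA reports: (2/32)[0.797 × 2(1 − ρ) + 0.203 × (1 − ρ)²]. At ρ = 0.5: 0.0625 × [0.797 + 0.051] = 0.0530, SE 0.230.
- Ratio 0.230/0.273 = 0.84. The critical value 2.00 then acts like 2.00 × 0.84 = 1.69, for which the two-sided normal tail is about 9%.

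**5. Simulation, 20% missing per arm, no true effect, nominal 5%** (8,000 to 20,000 trials per setting):

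| EM model | ρ = 0.3 | ρ = 0.5 | ρ = 0.7 |
|---|---|---|---|
| with group | 0.094 | 0.100 | 0.103 |
| separately by arm | 0.093 | 0.098 | 0.108 |

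Reported SE divided by true SD is 0.82 to 0.87 in these runs, and coverage is about 0.90. A repeat with 10,000 trials per setting gave type I error 0.093 to 0.108 and ratios of 0.82 to 0.85. With EM on the pooled file without group, type I error is 0.050 to 0.051 and the ratio is 0.99 to 1.00.

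**6. True effect of 0.82 SD.** Without group, the filled-in scores carry almost no group difference, so the expected estimate is about 0.82 × (1 − 0.203) = 0.65 SD. Simulation at ρ = 0.5 gives 0.65, power 0.79 and coverage about 0.89 to 0.90. Over ρ from 0.3 to 0.7, coverage runs from about 0.84 (ρ = 0.7) to 0.91.

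**7. Sensitivity, group in the model.** At ρ = 0.5, type I error is about 7% with 10% missing and about 8% with 15% missing. Over ρ = 0.3 to 0.7, adding residual noise still leaves 0.083 to 0.097. Loss of 40% in the MQT-SH arm and none in the control arm gives 0.104 to 0.119 (group in the model or by arm).

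**8. Proper handling.** Multiple imputation with group in the model and Rubin's rules (20 imputations): type I error 0.048 to 0.053; at ρ = 0.5 and the planned effect, power 0.83 and coverage 0.950. Observed cases only: type I error 0.050 to 0.055, power 0.82, coverage 0.951.

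**The case against.** The best defence is that the article is a condensed account. It never says that imputation is single, and the choice of imputation variables could sit in a fuller plan. That stands as far as it goes: the missing list of variables is not the fault here. The fault is that a named fill-in method is paired with a named test that takes the filled-in values at face value.

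A reader might infer that the type I error is simply doubled. The document does not support that, because it does not say whether group enters the EM model; on the pooled file the test keeps its 5% size. For the same reason it would be wrong to say that no version gives a valid test. Pooled EM is a valid test of no effect, with little loss of power (0.79 against 0.82 to 0.83). What fails there is the estimate and its interval. The two errors also run in opposite directions, one anti-conservative and the other conservative.

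The 20% is a planning allowance and actual loss may be smaller, which would shrink both errors. It may also be unequal: section 2.4.1 counts attendance at three or fewer of six sessions as dropout, which cannot apply to the waiting-list arm before T2.

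**Conclusion.** The concern holds, with its consequence conditional on the EM model. As written, the main analysis treats estimated T2 scores as data. At the plan's own 20% dropout this means one of two things:

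- Group in the EM model, or EM by arm: standard error about 13-19% too small, type I error about 9-11%, coverage about 90%.
- Pooled EM without group: type I error about 5%, effect diluted by about 20%, coverage about 84-91% at an effect of 0.82 SD.

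The ranges rest on an assumed correlation of 0.3 to 0.7 and on scores missing completely at random. Under either reading, the nominal 95% interval at the planned effect falls short of its stated coverage, so the method should be changed before analysis.

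**What to change.** In section 2.13, replace the EM fill-in by one of the following:

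- a likelihood-based mixed model on the observed T1 and T2 scores of all randomised participants, with the group-by-time interaction as the test; or
- multiple imputation with group in the imputation model, combined by Rubin's rules, with the imputation variables named.

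Either keeps all randomised participants in the analysis. The change needs new analysis wording and standard software, and no change to recruitment or sample size. Intervals will be somewhat wider than those from EM with group in the model, which is the correct width. At correlation 0.5, power stays at about 81-83%, in line with the stated 80%.

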The control group in this study is a non-active group. For ethical reasons, the control group will perform MQT-SH for six weeks between the T2 and T3 assessments. Therefore, the main statistical analysis is a comparison of the two groups for T1 and T2 assessments. Additionally, a follow-up effect analysis will be conducted in the experimental group alone, and a single-arm pre-post effect analysis will be conducted in the control group. Finally, a subgroup analysis will be conducted based on the amount of home training.

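### The main group-by-time ANOVA is valid but is a change-score test; estimating the baseline slope (ANCOVA on T1) would be more precise and needs no extra data

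*Protocol article*

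**What the plan says.** Section 2.13 (Statistical analyses) of the protocol article sets the efficacy test as a 2 × 2 design with group and time (T1, T2) as factors: "repeated measures ANOVA will be performed. If the interaction between the group and time is significant, a simple main effect analysis will be performed". The Discussion (section 3) confirms that this is the main comparison, because the control arm receives the programme after T2: "Therefore, the main statistical analysis is a comparison of the two groups for T1 and T2 assessments". Section 2.5 (Sample size) plans on the same test, "considering the existence of a significant 2 (group: experimental *vs*. control) × 2 (time: T1 *vs*. T2) interaction effect".

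Table 2 in section 2.8 shows every primary and secondary outcome measured at T1. No section adjusts for baseline. Section 2.6 gives the allocation as: "Participants will be randomly allocated to either the experimental or the control group (1:1 ratio, block size = 4". It mentions no stratification.

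**The concern.** A two-group, two-occasion interaction compares mean change between the arms. A change score uses baseline, but with its coefficient set to 1. If the true slope of T2 on T1 is below 1, subtracting the whole baseline score adds noise, and a chance difference between arms at T1 carries into the estimate through regression to the mean. ANCOVA estimates the slope from the same two measurements.

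At stake is the precision of each between-arm comparison in a trial with 32 participants per arm. The primary hypothesis at the end of the Introduction is a comparison with the control group, so the between-arm contrast is the one that should be estimated as well as the data allow.

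**Working it through.** **Inputs from the documents.** Section 2.5 gives power and error ("The sample size calculation is based on a power of 80% and a type I error of 5" per cent), effect size ("as well as a moderate effect size for the intervention (partial *η*^2^ = 0.04") and numbers ("A minimum sample size of 25 participants per group is estimated (50 participants in total"; "Considering a dropout rate of 20%, we aim to include 32 participants per group (64 participants in total").

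**Inputs assumed.** The T1–T2 correlation r is not stated, nor are the standard deviations. The test is taken as the 1-df F test, that is, a two-sided t.

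**Step 1: reproduce the plan's figure.** f² = 0.04/0.96 = 0.0417, so f = 0.204. For the interaction with two occasions, λ = N × 2 × f²/(1 − r), with df 1 and N − 2. At r = 0.5 and N = 50, λ = 50 × 2 × 0.0417/0.5 = 8.33 and power is 80.7%; 50 is the smallest even N reaching 80%. On a grid of r in steps of 0.1, no other value returns 50: 0.3 gives 68, 0.4 gives 60, 0.6 gives 40 and 0.7 gives 32. For dropout, 25/0.8 = 31.25, rounded up to 32 per arm. The plan's figures therefore reproduce at r = 0.5.

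**Step 2: restate as a change-score test.** In units of a common SD, the variance of change is 2(1 − r) = 1.0 at r = 0.5. From λ = (N/4) × d²/1.0 = 8.33 at N = 50, d = 0.816 SD.

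**Step 3: compare variances.** With SDs s1 and s2:
- change: s1² + s2² − 2·r·s1·s2
- ANCOVA residual: s2²(1 − r²)
- difference: (s1 − r·s2)², which is never negative.

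With s1 = s2, the ratio of ANCOVA to change variance is (1 − r²)/[2(1 − r)] = (1 + r)/2, which is 0.75 at r = 0.5.

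**Step 4: power at r = 0.5, equal variances.** At N = 50, ANCOVA has λ = 8.33/0.75 = 11.1 with df 1 and 47. Power is 90.4% by formula and 89.7% by simulation (40,000 replicates), against 80.7%. At N = 64 with all participants contributing, power is 96.0% against 89.5%. Simulated type I error, checked at N = 50 for r from 0.3 to 0.9, was between 4.9% and 5.3% for both tests.

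**Step 5: range over r.** The effect is rescaled at each r so that the change-score test keeps about 80.7% power at N = 50; variances are equal.

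| r | variance ratio | ANCOVA power, formula | ANCOVA power, simulation |
|---|---|---|---|
| 0.3 | 0.65 | 93.9% | 93.3% |
| 0.5 | 0.75 | 90.4% | 89.8% |
| 0.7 | 0.85 | 86.6% | 85.7% |
| 0.8 | 0.90 | 84.6% | 83.7% |
| 0.9 | 0.95 | 82.7% | 81.8% |

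**Step 6: unequal variances (illustrative).** With k = s2/s1, the ratio is k²(1 − r²)/(1 + k² − 2rk).
- r = 0.7, k = 1.2: 0.734/0.76 = 0.97.
- r = 0.7, k = 1.4: the slope is 0.7 × 1.4 = 0.98 and the ratio is 0.9996/1.00, so the gain is nil.
- r = 0.5, k = 1.5: 1.6875/1.75 = 0.96.
- If T2 spread is the smaller, (s1 − r·s2)² grows and so does the gain.

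**Step 7: chance imbalance.** At 32 per arm, the standard error of the baseline difference is √(2/32) = 0.25 SD. At r = 0.5 with equal variances, an imbalance of one standard error shifts the change-score estimate by (1 − 0.5) × 0.25 = 0.125 SD, or 0.125/0.816 = 15% of the planned effect. ANCOVA corrects for this shift.

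**The case against.** The plan is coherent: it is sized on the interaction, analyses the interaction and names that comparison as the main one. The planned test is unbiased under randomisation, keeps its level and reaches the stated power. All of that stands, and it makes this an efficiency point. The imbalance in step 7 is likewise a conditional effect in a particular sample; over repeated randomisations the change-score estimate is unbiased.

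The gain also depends on quantities the article does not give. The 0.5 is inferred from the sample size, and the equal-variance assumption matters. Section 2.3 requires both diagnoses at entry, which could narrow the T1 spread relative to T2 and reduce the gain. This stands too, and is why a range is shown. It does not reverse the direction: ANCOVA loses nothing beyond the small cost of estimating one slope, one error degree of freedom.

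Three stronger readings are tempting but unsupported:
- **That the plan throws baseline information away.** It uses baseline, with the slope fixed at 1.
- **That inference moves to within-arm comparisons.** Section 2.13 makes a simple main effect analysis conditional on a significant interaction but does not say which simple effects are meant. They could equally be the group difference at T2, and the between-arm test remains the interaction.
- **That the trial is wrongly sized or should be made smaller.** The sample size reproduces. ANCOVA would need about 38 to 40 participants for 80% power at r = 0.5, but recruitment and treatment have started (section 3.3), and that figure rests on an unstated correlation.

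An unseen analysis plan does not fully answer the point, because the article itself names the test.

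**Conclusion.** The concern holds as an efficiency weakness that should be corrected. It is not an error that invalidates the analysis. At the correlation that reproduces the plan's own sample size, and with equal T1 and T2 variances, the change-score test gives up 9 to 10 percentage points of power at 50 participants. With change-score power held at about 81%, the formula gain is about 13 points at r = 0.3, 6 at 0.7, 4 at 0.8 and 2 at 0.9. It can be near nil if T2 variance is much the larger. Since precision is not lost in any of these cases beyond one degree of freedom, and T1 is already measured for every outcome, there is no statistical reason to prefer the fixed slope.

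**What to change.** Before outcome data are examined, amend section 2.13 so that the primary analysis of each outcome regresses the T2 score on arm and T1 score (ANCOVA, or an equivalent mixed model with the baseline means constrained equal, which also accommodates missing T2 values). Report the adjusted between-arm difference with its 95% CI and p-value as the inference. Present simple effects descriptively only, and say which ones are meant. Align the sentence on the main analysis in the Discussion.

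Keep the sample size at 64. No new data or participants are needed. The cost is a dated, documented wording change and the IRB review that the Ethics statement requires for protocol changes. Because the trial is under way, the record should show that the change preceded any look at outcomes.
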